## **10.0 BIBLIOGRAPHY**

## **11.0 APPENDIX I – Script utilized to describe the conceptual basis of the placebo effect**

## 1.0 BACKGROUND

In 2014, 47,055 drug overdose deaths occurred in the United States, and 61 percent of these deaths were the result of opioid use, including prescription opioids and heroin—a near-quadrupling of opioid-related deaths since 1999. The incredible surge in deaths owing to Opioid Use Disorder (OUD) has caused many federal and state agencies to identify a “heroin epidemic”—a crisis facing our nation so great that it is considered by many to be one of the largest looming threats to public health today. Methadone treatment (MT) is the most highly researched and evidence-based treatment for OUD and has become the mainstay for the treatment of opioid dependence with strong scientific recommendation for continued widespread availability. By binding to  $\mu$ -opioid receptors, methadone works to alleviate opioid withdrawal. Yet there is great individual variability in MT response. While many patients have positive outcomes with low to moderate doses of methadone (e.g., ~30 mg/day), effectively allowing them to maintain sobriety for years on end, most patients need much higher doses of methadone to maintain their craving and drug-seeking behavior. Unresolved medical debates on whether “more is better” provide no clarity on this issue, and with no generally accepted optimal dose prescription, clinicians titrate MT dose to a subjective patient behavioral effect—a practice that often translates to the prescription of very high doses of methadone, affecting both treatment cost and public health policy.

These higher doses of methadone come at an unfortunate cost and are associated with a long list of common side effects and cardiotoxicity. High-dose MT side effects include constipation, sedation, nausea, and sweating, and are often severe enough to drive many patients to quit their MT program. Adams reported that in a study of treatment failures, 27% of the patients on high-dose methadone reported side effects as a primary reason for leaving treatment. In rare cases, severe cardiac effects have been reported, and cases of QT interval prolongation and Torsade de pointes (a cardiac arrhythmia characterized by rapid, irregular QRS complexes)-have been reported in patients taking very high doses of methadone, underscoring the risk associated with high-dose MT. Reports of increasing methadone-related deaths have only fueled this risk awareness, and have led to greater scrutiny of methadone dosing practices. Finally, an estimated 30% of MT patients have severe anxiety related to MT detoxification due to fear of withdrawal and relapse: concerns that theoretically could be eased by the implementation of treatment paradigms incorporating low-dose MT. Collectively, these various

issues provide a compelling rationale to explore plausible options to increase the therapeutic window of low-dose methadone.

Recent investigations have yielded greater appreciation of the therapeutic potential of the placebo response. Increasingly more research has turned its focus to study ways in which to ethically harness that potential, and two main strategies have dominated these discussions. One stream of research employs principles of Pavlovian conditioning. By pairing placebo pills and clinical contextual cues (conditioned stimuli) with a physiologically active treatment (unconditioned stimuli), researchers have shown that medication dosages can be lowered without decreasing treatment efficacy. For example, Ader and colleagues demonstrated that placebos extend the effects of corticosteroids in psoriasis patients when given in accordance with a partial reinforcement paradigm. The frequency of disease relapse under this partial reinforcement paradigm was lower (26.7%) than in the control group (61.5%), outcomes which were clinically comparable to the reduction in symptoms induced by a full-dose regimen of corticosteroids (22.2%). Similarly, Perlis and colleagues applied a reinforced therapeutic schedule to medically manage chronic insomnia using 10 mg zolpidem pill with 50% active medication and 50% placebos for 12 weeks. The partial reinforcement group showed the same clinical benefit as the groups randomized to 10 mg or 5 mg or intermittent 10 mg nightly dosing. In a separate study, children with Attention Deficit Hyperactivity Disorder (ADHD) showed a therapeutic benefit when placebo pills were paired with a 50%-reduced dose of amphetamine. Thus, pairing a conditioned stimulus with amphetamines, corticosteroids, or zolpidem produced placebo conditioned responses that allowed individuals to be treated effectively with lower doses of the active medication. To date, this associative learning methodology has not been tested on methadone treatment or pain syndromes.

A second strategy to ethically harnessing placebo effects is known as “open-label placebo” administration. In most of these studies, patients in research settings are given placebo pills in an honest and transparent manner, and are told something in accord with, “we know that placebos have powerful effects in double-blind trials, and we want to test whether placebos work even if a patient knows they’re taking placebos.” Several such experiments have yielded positive results on conditions such as irritable bowel syndrome, chronic low back pain, migraine headache, allergic rhinitis and depression. Open-label placebo administration circumvents many of the ethical problems historically associated with traditional (deceptive) placebo use, including disrespect of patient autonomy, threats to a clinician’s integrity, and

potential damage to societal trust in the medical profession. Yet no study has investigated the efficacy of open-label placebo strategies in a methadone maintenance context. The proposal we submit uniquely combines both approaches.

## **2.0 PROJECT OVERVIEW**

**2.1 Brief project overview.** The broad goal of this proposal is to enhance treatment outcomes for OUD patients enrolled in a daily outpatient MT program. We will combine two well-known protocols for inducing placebo effects. Implementing principles of pharmacological conditioning, we will temporally pair placebo pills with the oral methadone solution that is provided to patients at the clinic, to ultimately use placebos as a conditioned stimulus. Additionally, we will apply an open-label paradigm: we will give the participants information concerning the placebo pill in an honest and transparent manner. This unique approach of combining two powerful protocols (pharmacological conditioning and open-label design) capitalizes on methods that have been robustly shown to enhance treatment outcomes in other patient populations. This proposal will allow us to conduct a proof-of-concept study to harness placebo effects with the ultimate scope of enhancing medication-based clinical treatment of Substance Use Disorder and minimizing methadone escalation.

**2.2 Specific Aims.** SA1: To compare the impact of pharmacologically conditioned open-label placebo to Treatment as Usual (TAU) on ultimate methadone dose achieved at 90 days. SA 2: To assess the effects of conditioned open-label placebo administration on 90-day MT outcomes and patient retention.

**2.3 Significance.** The findings obtained from these studies will provide crucial pilot data concerning the effectiveness of placebo interventions implemented in the context of substance use disorders, heretofore unexamined. Additionally, the data will contribute importantly to the growing literature on the translational applications of laboratory findings of manipulations involving the placebo effect in clinical practice by exploring a placebo effect in study participants with substance use disorder. To our knowledge, no data such as this exists in the drug addiction literature. If successful, this project will yield pilot data that will allow us to apply for larger funding opportunities using neuroimaging methodologies, with an aim to explore the mechanisms that underlie the placebo phenomenon in individuals with substance use disorders.

## **3.0 FACILITIES AND RESOURCES**

**3.1 University of Maryland Addiction Treatment Center (UMATC).** The clinical site for the proposed project is the University of Maryland Addiction Treatment Center (UMATC), an urban outpatient (Level-1) drug treatment center based at the University of Maryland in Baltimore, MD. The UMATC is accredited by the Commission on Accreditation of Rehabilitative Facilities, International (CARF) and certified by SAMHSA as an opioid treatment program (OTP). It is a Maryland Department of Health and Mental Hygiene-certified Opioid Treatment Program that provides Level I (outpatient) treatment services. As the first hospital-based methadone program in the state of Maryland (founded in 1972), the UMATC has long embraced a tradition of folding rigorous, empirically validated approaches into comprehensive strategies for the treatment of OUD – a tradition that has served as the philosophical cornerstone for all clinical programming. Additionally, the Division has been an integral collaborator with the Baltimore Buprenorphine Initiative since its inception in 2006. The UMATC has been located at its current site since 2012. The program is centrally located and accessible by public transportation (MTA and Charm City Circulator) and contains ample free parking. The clinic is approximately 15,000 square feet and offers all three FDA-approved forms of MOUD (methadone, buprenorphine and vivitrol) along with individual and group counseling and psychiatric services. The UMATC utilizes an interdisciplinary treatment team which includes: a family medicine/addiction medicine physician, three licensed addiction psychiatrists, one Nurse Practitioner, a full-time psychologist, three registered nurses, five LPNs, two medical attendings, 11 counselors, one social worker, a peer recovery specialist, one clinic director, three administrative staff members and one program manager (who is also a licensed counselor). The UMATC's quality assurance reviews include the quarterly review of staff licensure and credentials as well as monthly Office of the Inspector General Exclusion List reviews.

**3.2 UM School of Pharmacy Good Manufacturing Practice Facility (GMPF).** Placebo pills used in this program will be produced by the GMPF. The facility has three 500 square-foot research laboratories, one 500 square-foot GLP laboratory, and six GMP pharmaceutical manufacturing suites. It also includes rooms for the receipt and storage of GMP materials. The labs are equipped to perform pre-formulation research, excipient screening, physical characterization of polymorphs, formulation and process development, GMP manufacturing, packaging and labeling. The analytical labs are equipped for methods development, testing and validation. There are also validated stability cabinets to conduct stability studies in accordance with International Council for Harmonization of Technical Requirements for Pharmaceuticals for

Human Use (ICH) guidelines. For this project, placebo pills will be composed of microcrystalline cellulose PH-102, magnesium stearate, and D&C Red 7 Ca Lake (inert chemicals and a food colorant, ingredients commonly contained in placebo pills manufactured by the pharmaceutical industry). Placebo pills are stored in a locked medications cabinet maintained within the nurses' station at the UMATC.

#### **4.0 CLINICAL OUD DIAGNOSIS AND TREATMENT**

Methadone is dispensed daily Monday through Saturday with a take-home dose given for Sunday. All patients admitted to the methadone program are assessed by a nurse practitioner and a board-certified addiction medicine physician and are initiated on a standard protocol for treatment of OUD with methadone. Initial methadone doses are individualized with a typical starting dose of 25-30 mg/day that is increased by 5 mg every other day to a targeted holding dose (~80-120 mg). All dose increases are discussed with the treatment team and approved by the OTP's medical director. Patient dosing encounters are logged in the clinic's electronic health record management platform (Methasoft, Netalytics, Greer, NC) and can be accessed for information relevant to treatment retention. Per standard clinic operating procedures, and in line with SAMHSA methadone dosing guidelines, patients missing two or more consecutive days of treatment had their doses reduced (up to 50%) to ensure safe prescribing. Patients who miss 30 consecutive days of dosing (no-call/no-show) are administratively discharged and considered not retained. Urine toxicology is obtained monthly as standard-of-care per state regulations, is recorded in Methasoft, and includes tests for opiates, oxycodone, and fentanyl. In addition to treatment with medications, the clinic provides counseling, psychiatric, basic primary (wound) care, and social work and health home services. Most patients reside within one of five zip codes that immediately surround the clinic address, and present to the clinic either by referral or self-admission. Approximately 4-8 new patients are admitted into the methadone program per week.

#### **5.0 RESEARCH DESIGN AND METHODS**

**5.1 Overview of study design.** We propose to conduct a proof of principle investigation to test the impact of a conditioned, open-label placebo intervention on methadone treatment outcomes. One-hundred twenty new intakes into methadone treatment for OUD will be approached, consented, and randomly assigned to one of two conditions: conditioned open-label placebo (group C-OLP) plus methadone or methadone/Treatment as Usual (TAU). We will follow them

for three months for a total of five in-person meetings (baseline, two weeks, and 1-, 2- and 3- months post-baseline). For the first two weeks, we will implement principles of pharmacological conditioning whereby placebo pills are temporally paired with the oral methadone hydrochloride solution that is provided to patients at the clinic (conditioning phase). Having established an association and contextualized the placebo as part of the therapeutic experience, placebos are then used as a dose extension pill (week 3 up to three months). Additionally, we are applying an open-label paradigm, giving participants information concerning the placebo pill in an honest and transparent manner. Our primary outcome is methadone dose three months after (baseline) entry into treatment; secondary outcomes include several measures of treatment success including comprehensive urine toxicology screens, self-reported drug use, and treatment retention. We are also capitalizing on this unique patient access opportunity to measure several personality and environmental factors associated with OUD, as well as factors associated with placebo response. A complete schedule of all study-related procedures is presented in Table 1.

| Table 1. Assessment timeline                 |                     |                            |             |                        |             |             |
|----------------------------------------------|---------------------|----------------------------|-------------|------------------------|-------------|-------------|
|                                              |                     | Phase I
(Weeks 1 and 2) |             | Phase II
(Weeks 3+) |             |             |
|                                              |                     | Meeting (Day Number)       |             |                        |             |             |
| Activity/
Instrument                      | Time to
Complete | 1
Day 0                 | 2
Day 14 | 3
Day 28            | 4
Day 56 | 5
Day 84 |
| Verbal assessment of
participant interest | 1 minute            | X                          |             |                        |             |             |
| I/E confirmation                             | 1 minute            | X                          |             |                        |             |             |
| Informed Consent (IC)                        | 5 minutes           | X                          |             |                        |             |             |
| HIPAA Authorization                          | 2 minutes           | X                          |             |                        |             |             |
| IC Evaluation                                | 3 minutes           | X                          |             |                        |             |             |
| Study Script                                 | 3 minutes           | X                          |             |                        |             |             |
| Placebo Effect Video                         | 2 minutes           | X                          |             |                        |             |             |
| Pill Information Sheet                       | 1 minute            | X                          | X*          | X*                     | X*          |             |
| Day Expectancy
Assessment                 | <1 minute           | X                          |             |                        | X           | X           |
| Past 2-Week Drug Use
Assessment           | 2-3 minutes         | X                          | X           | X                      | X           | X           |

Conditioned Opel-Label Placebo for Methadone Treatment of Opioid Use Disorder: A Single-Blind  
Randomized Clinical Trial  
Trial Protocol  
Effective Date: July 27, 2017

|                                       |             |   |   |   |   |   |
|---------------------------------------|-------------|---|---|---|---|---|
| BIS/BAS                               | 8 minutes   | X |   | X |   | X |
| Pain Catastrophizing Scale            | 5 minutes   | X |   | X |   | X |
| Pittsburgh Sleep Quality Index        | 6 minutes   | X |   | X |   | X |
| Cleveland Clinic Constipation Scoring | 5 minutes   | X | X | X | X | X |
| WHO Quality of Life Assessment        | 10 minutes  | X | X | X | X | X |
| Craving Assessment                    | <1 minute   | X | X | X | X | X |
| SOWS                                  | 5 minutes   | X | X | X | X | X |
| OOWS                                  | 5 minutes   | X | X | X | X | X |
| Baseline Drug Use History             | 10 minutes  | X |   |   |   |   |
| Randomization                         | 1 minute    | X |   |   |   |   |
| Order Form*                           | 1 minutes   | X | X | X |   |   |
| Urine Sample                          | 3 minutes   | X | X | X | X | X |
| Payment Logs                          | 3 minutes   | X | X | X | X | X |
| Placebo Compliance*                   | <1 minute   |   | X | X | X | X |
| Methadone Side Effects Checklist      | 5-7 minutes |   | X | X | X | X |
| Monetary Choice Ques.                 | 4 minutes   |   | X |   | X | X |
| BIS-11                                | 8 minutes   |   | X |   |   |   |
| Post-Baseline Drug Use History        | 5 minutes   |   | X | X | X | X |
| Exit Interview                        | 4 minutes   |   |   |   |   | X |

\*Indicates assessments that were administered only to participants in Placebo (C-OLP) Group

293 **5.2 Study population.** Study participants will be 120 men and women OUD adults newly  
294 admitted to the UM Addiction Treatment Center (UMATC). Over half of the patient population  
295 receiving treatment at the UMATC identify as Black or African American (53.1%) and male  
296 (55.8%). New patients will be recruited on their first day of treatment in the clinic (Day 0).  
297 Subjects of all races and sexes will be included.

298 **5.3 Eligibility criteria.** Inclusion criteria include adults ( $\geq 18$  years old) meeting DSM-V criteria  
299 for diagnosis of moderate-to-severe OUD who are new initiates for treatment with methadone

medication. Exclusion criteria include pregnancy (confirmed with urinalysis), transfer into the clinic from another MT program or hospital, and court ordered treatment. These exclusions will be adopted to avoid extenuating factors that could potentially impact clinical treatment determinations or outcomes.

**5.4 Recruitment and informed consent.** New patients will be recruited on the first day of treatment in the clinic (Day 0). At the end of their initial intake procedures of their first day, patients will be asked if they are interested in hearing information about a study that is testing a novel approach to enhancing methadone treatment, for which they would receive paid compensation. The PI will contact the intake coordinator by 9:00 AM to receive a list of patients who are new intakes to the clinic and who are willing to hear about the study. Those patients who indicate their interest will be approached by the PI (or the study research assistant) later that morning as they are awaiting their methadone dosing in the waiting area of the clinic (normal waiting times vary from between 30 minutes to an hour, providing ample time for a consent and scripted recruitment). At this point, the PI will introduce herself, and will assess interest in study participation. Interested patients will be directed to a small interview room located proximal to the waiting area, and a few steps from the nurses' station. The door will be closed, and the investigator will determine whether the patient meets study eligibility criteria (I/E confirmation), and if so, will obtain informed consent and an authorization for release of Health Insurance Portability and Accountability Act (HIPAA) information for specific data related to OUD treatment. The investigator will then assess comprehension with an Evaluation to Sign Consent form (IC Evaluation). Participants will be asked to provide a suitable method of contact (phone number, e-mail, or consent to be contacted through a flag placed on the person's name in Methasoft, the electronic health record platform used at the UMATC). At the end of the baseline meeting, participants will be given an appointment reminder card with follow-up meeting dates for the 4 return visits. On the day prior to each of these meeting dates, contact will be made with the participant to remind him/her of the next scheduled appointment with the study team.

**5.4.1 Script and study information provided.** Patients are fully debriefed of all study procedures during the informed consent process. Participants are informed that their participation in the trial will have no effect on ongoing treatment afforded by the clinic, and further, that they have the right to withdraw from the study at any time with no impact on their clinical treatment. During and following consent, the notion is reinforced to the patients that the

research study is “designed to investigate the efficacy of methadone treatment that is enhanced via inner healing processes using placebo effects.” A script will be used as a conversational guide to inform patients of the study rationale and procedures (Appendix I). This script has a positive framing and describes in lay terms the science that underlies placebo effects and pharmacological conditioning, with an aim to facilitate the placebo response in a non-deceitful manner. Following the conversational reading of the script, the investigator will ask the participant to view a video of a CBS New York News piece that describes scientific studies of the successful use of the placebo phenomenon as a therapeutic intervention for irritable bowel syndrome. The participant then completes the Day 0 (baseline) assessments. As a final step (and to ensure equal investigator/participant time), prior to treatment allocation, the investigator will give the participant a placebo pill information sheet. This handout will contain explicit instructions on how to take the pill, the pill’s formulation, and the contact information for a study team member who will be able to answer any questions that the participant may have about the placebo pill or the study.

**5.5 Randomization and treatment allocation.** Prior to study inception, random treatment allocation will be generated by an independent investigator in unequal block fashion (60:40 intervention:control). Randomization consists of sequentially numbered opaque envelopes containing treatment assignments drawn from a computer-generated random number sequence. These numbers are used to assign participants to either C-OLP or TAU. Two stacks of envelopes will be created to ensure an even distribution of men and women (N=30/group/sex for a total of 120 random treatment allocations).

Treatment allocation occurs after completion of all Day 0 (Baseline) assessments. The investigator performs allocation by pulling an envelope from the top of the sex-specific stack. Following Day 0 study procedures, and just prior to the first dose of methadone at the treatment window, the investigator conducts a treatment assignment “reveal,” opening the envelope and letting the patient know the group to which s/he has been assigned. Group assignment will be revealed with the words: “Great, you’re in the placebo group,” or “Great, you’re in the Control, or Treatment-As-Usual group.”

**5.6 Placebo intervention.** Placebo pills are produced by the University of Maryland School of Pharmacy Good Manufacturing Practice facility. The pills are composed of microcrystalline cellulose PH-102, magnesium stearate, and D&C Red 7 Ca Lake (inert chemicals and a food colorant, ingredients commonly contained in placebo pills manufactured by the pharmaceutical

industry). Placebo pills are stored in a locked medications cabinet maintained within the nurses' station.

Following treatment assignment on Day 0, the investigator fills a placebo pill dispensing form indicating treatment assignment, and the patient is walked to the methadone dosing station. Placebo pills are stored and dispensed by the nursing staff of the UMATC. If the patient is in group C-OLP, the investigator observes the participant taking the placebo pill. In Phase 1 of the study (first two weeks), participants assigned to C-OLP are given one pill, to be taken concomitant with the methadone. In Phase 2 (3 weeks up to 3 months), C-OLP participants continue to take the single (morning/AM) pill and are given a second pill in a bottle as a take-home. They are instructed to take this second pill twelve hours following the first pill, "at home, or wherever they may be." Participants will be asked to return the take-home pill bottle every day for refill. Participants assigned to TAU will also be walked to the methadone window for observed dosing but will not receive a placebo pill. Following dosing, participants will be paid for their participation, and reminded of their next appointment in two weeks.

**5.7 Post-baseline meetings with study team.** Following the initial (baseline, Day 0) meeting, all participants will be asked to meet with a member of the study team at the following intervals: 14-, 28-, 56-, and 84-days following intake, periods of time that roughly correspond to 2 weeks, 1-, 2- and 3-months of treatment. Participants will be paid \$25 for each 30- to 45-minute study visit, for a total possible \$125. Because study participants are clients of the UMATC, they must come to the clinic daily for the first several months of their OUD treatment, facilitating follow-up with the study team (the research study team is co-located at the UMATC).

**5.8 Blinding.** At all stages of the study, methadone dose adjustments are conducted by an independent clinician blinded to treatment allocation and to when a participant is enrolled in the study. Additionally, because treatment allocation occurs only after Day 0 (baseline) assessments are complete, study team members are blind to treatment assignment for all of Day 0 procedures. Finally, data analysts are blind to treatment allocation.

**5.9 Urine toxicology screens.** Urine drug screening will occur *via* two methods: (1) a point-of-care Quik-tox screen (11 panel; LabCorp) conducted by clinic staff, results of which are reported immediately, conducted at baseline and then at monthly (random) intervals post-baseline; (2) and liquid chromatography–tandem mass spectrometry (LC-MS/MS) testing for a panel of more than 240 drugs, including new psychoactive substances, as well as other illicit and prescription

drugs. All testing is conducted by the Division of Forensic Toxicology, Armed Forces Medical Examiner System and coordinated by the University of Maryland, College Park Center for Substance Abuse Research (CESAR) staff. Urine is collected from participants during each of the five meeting times, and the Quik-tox screen is conducted only on samples from meeting one (baseline); the LC/MS/MS testing is conducted on all samples (baseline and 2 weeks, and 1-, 2- and 3-months post-baseline screening).

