## **7.0 DATA ANALYSIS**

**7.1 Sample size calculation.** We anticipate that dose escalations will be recommended at dose evaluation (approximately three weeks following entry into treatment) for approximately 70% of participants in the TAU control group. With 60 participants per group, we will have power of .80 to detect a difference between groups if the corresponding rate in the intervention group is 44% or lower (i.e., a maximum of 26/60 participants), using a Fisher exact test with a two-tailed alpha of .05. This is a medium-to-large effect, equivalent to an odds ratio of 3.03 or a Cohen's d of .61.

**7.2 Data analysis plan for pre-specified primary outcome of methadone dose.** Descriptive statistics with central tendencies and spread will be used for continuous variables; distributions and percentages will be used for categorical variables. Group differences in mean dose of methadone (in milligrams) at 90 days (primary outcome) will be tested with unpaired t-tests.

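### Allocation is stratified by sex, but the primary t-test on 90-day methadone dose ignores sex, which makes the interval slightly too wide if sex predicts dose

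*Protocol*

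**What the plan says.** Protocol Section 5.5 sets up the allocation by sex: "Two stacks of envelopes will be created to ensure an even distribution of men and women". It adds the intended cell sizes, "N=30/group/sex for a total of 120 random treatment allocations", and says how the envelopes are used: "The investigator performs allocation by pulling an envelope from the top of the sex-specific stack". Sex is therefore a stratification factor in the ordinary sense.

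Section 7.2 names the primary test: "Group differences in mean dose of methadone (in milligrams) at 90 days (primary outcome) will be tested with unpaired t-tests". It mentions no stratum and no covariate. Section 7.3.1 gives a chi-square test for retention. Section 7.3.2 writes out a mixed model whose terms are baseline, arm by visit and a subject effect. Sex appears in none of these.

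Table 1 places SOWS, OOWS, craving and past-two-week drug use on Day 0, and Section 5.5 puts allocation after all Day 0 assessments. These values are therefore free of any influence of the assigned arm.

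**The concern.** Stratifying by sex gives the two arms nearly the same mix of men and women, so a sex difference in dose cannot contribute to the difference between arms. An unpaired t-test does not know this. It estimates its error from the full spread of doses within each arm, including the spread between men and women. If sex predicts dose, the reported standard error is larger than the true one, the interval is wider than it should be, and the test rejects less often than its nominal 5%.

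A second, separate matter is that Day 0 values already in hand are not used. That omission does not bias the standard error. It only forgoes whatever precision those values could bring.

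What is at stake is efficiency in a trial of 120 participants, not protection against false positives.

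**Working it through.** **The plan's own figure.** Section 7.1 states: "With 60 participants per group, we will have power of .80 to detect a difference between groups", for rates of 70% and 44% (at most 26/60), by a two-sided Fisher exact test at 0.05. Full enumeration of both binomials gives power of 0.785 at 44% and 0.806 at 26/60. The odds ratio is 2.97 to 3.05, and d = ln(OR)·√3/π is 0.60 to 0.615. The stated 0.80, 3.03 and 0.61 are reproduced. That calculation concerns dose escalation at about three weeks, not 90-day dose, so nothing below changes it.

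**Inputs.** From Section 5.5: 30 per arm per sex, hence 60 per arm. From Section 7.2: an unadjusted two-sample comparison of means. Assumed: R², the share of variance in 90-day dose explained by sex. The Protocol gives no SD of dose and no relation between sex and dose, so R² is taken over 0 to 0.10.

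**Formulas.** Let σ² be the total within-arm variance of dose.
- Variance that the t-test assumes for the difference: σ²·(2/60).
- True variance under stratification: (1 − R²)·σ²·(2/60), because the sex component cancels between arms with the same sex mix.
- Interval width, unadjusted over sex-adjusted: 1/√(1 − R²).
- Actual alpha of the t-test: 2·[1 − Φ(1.96/√(1 − R²))].
- Power at standardised difference d, with SE = √(2/60) = 0.183: unadjusted Φ((d/SE − 1.96)/√(1 − R²)); adjusted Φ(d/(SE·√(1 − R²)) − 1.96). Here d = 0.511, the value that gives 80% power when R² = 0: (1.96 + 0.84)·0.183 ≈ 0.51.

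The alpha formula was checked with 200,000 simulated trials per R² value at 30 per arm per sex.

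| Assumed R² for sex | Width ratio | 1.96/√(1 − R²) | t-test alpha, formula | t-test alpha, simulated | Sex-adjusted alpha, simulated | Power, unadjusted | Power, adjusted |
|---|---|---|---|---|---|---|---|
| 0 | 1.000 | 1.960 | 0.050 | 0.050 | 0.050 | 0.799 | 0.799 |
| 0.02 | 1.010 | 1.980 | 0.048 | 0.047 | 0.050 | 0.802 | 0.807 |
| 0.05 | 1.026 | 2.011 | 0.044 | 0.044 | 0.049 | 0.805 | 0.819 |
| 0.10 | 1.054 | 2.066 | 0.039 | 0.038 | 0.049 | 0.812 | 0.839 |

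The interval is thus 1.0%, 2.6% or 5.4% too wide, and the power forgone is 0.5, 1.4 or 2.7 percentage points. At R² = 0.10 the nominal 95% interval covers about 96.1%.

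**Allocation ratio.** Section 5.5 also describes the sequence as "in unequal block fashion (60:40 intervention:control"), which for 120 would be 72 and 48 rather than 60 and 60. The two statements need reconciling, but they do not affect this point. If the same ratio holds in both sex stacks, sex still cancels and the factor 1/√(1 − R²) is unchanged.

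**The case against.** The strongest reply is that an unadjusted t-test is a valid analysis for a proof-of-concept trial, that Section 5.5 gives balance as the purpose of the two stacks without calling sex prognostic, and that covariate choice is often left to a statistical analysis plan. Much of this stands. The t-test does not inflate the type I error here, and the loss is zero if sex is unrelated to dose. The argument about the analysis plan carries less weight, because the Protocol does not leave the method open: it names the primary test and prints the secondary model.

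Several stronger readings are tempting, and the documents do not support them.
- A reader might infer that the primary error bars are certainly wrong. That depends on sex predicting dose, for which no figure is given.
- A reader might infer that omitting any baseline value mis-states the error. Only the stratification factor can do so; the others bear on precision alone.
- A reader might assume that sex and baseline values together explain 20% of the variance, so that the interval would narrow by 11% (√0.80 = 0.894) and the gain would equal 30 participants (120/0.80 = 150). Nothing in the Protocol supports 20%, and the calculation treats all 120 as having a 90-day dose, although Section 6.2.1 provides for non-retention.
- A reader might take starting dose as the natural covariate. Section 4.0 says: "Initial methadone doses are individualized with a typical starting dose of 25-30 mg/day", which leaves little spread to work with. Table 1 lists no dose item, and Section 5.5 places the first dose after the assignment is revealed. The order may be written at intake, but the Protocol does not say so.

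It is also fair to note that the models in Section 7.3.2 already use the baseline value of each outcome.

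**Conclusion.** The mismatch between design and analysis is real and small. The Protocol stratifies by sex and then fixes a primary test that ignores sex. The consequence is conditional and conservative, as set out above, and is nil at R² = 0. The sizes rest on an assumed R², on both sexes being allocated in the same ratio, and on that balance surviving into the set with a 90-day dose, which dropout would make only approximate. They say nothing about the power stated in Section 7.1, which belongs to a different endpoint and test. This is a worthwhile improvement, not a threat to the validity of the primary conclusion.

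**What to change.** In Section 7.2, replace the unpaired t-test with a linear model of 90-day dose on arm and sex, plus a Day 0 measure named in advance and taken before allocation. Baseline SOWS is a reasonable choice: Section 1.0 describes dose as titrated to the patient's subjective response, although the Protocol does not quantify any link between SOWS and dose. Report the adjusted mean difference with its 95% confidence interval, and show the unadjusted difference as supportive. Sex can be added to the Section 7.3.2 models in the same way. Do not rely on starting dose as a covariate unless the Protocol is amended to show that it is fixed before allocation.

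The cost is a change of wording. Sex is known at allocation and SOWS is already collected, so no new data or visits are needed, and the model spends one degree of freedom per added term. Naming the covariates before the data are unblinded also rules out choosing them later by their effect on the result.
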